### Trial Design

In this proposed study, we will use a single-blind randomised controlled trial design with two-armed repeated measures. The trial design complies with the Consolidated Standards of Reporting Trials (CONSORT) statement (61). In our two-armed design, we will use TPS as an intervention group and a waitlist control group. At the same timepoints, we will appropriately compare the effect of the TPS treatment between those who received it in the intervention group and those who did not receive it in the waitlist control group (62). Both groups were measured at baseline (T_1_), immediately after the intervention (T_2_), and at the 3-month follow-up (T_3_). A total of 30 community-dwelling subjects, aged 18 and above, will be recruited. All subjects will be computer randomised into either the intervention group or the waitlist control group, balanced by gender and age on a 1:1 ratio. All subjects in each group will have to undertake fMRI before and after six 30-min TPS sessions, which will be completed in 2 weeks' time. Baseline measurements and post-TPS evaluation of the psychological outcomes (i.e., depression, cognition, anhedonia, and IADL) will also be conducted on all participants. Based on the previous studies, a 3-month follow-up is sufficient to assess the long-term sustainability of the TPS intervention (60).

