### Sample Size

#### Sample Size Estimation

To the best of our knowledge, there is only one TPS uncontrolled pilot study conducted on 35 patients with AD in Austria (60). Therefore, we cannot base on their effect size to estimate our sample size in this study. Considering the nature of our study is the first pilot RCT in using TPS in the treatment of depression, and also referenced by Beisteiner's study, we aim to recruiting 30 subjects to evaluate the efficacy of our primary and secondary outcomes in this study.

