## Assignment of Interventions: Allocation

### Sequence Generation

#### Randomisation, Allocation, and Masking

All consenting participants will be listed in alphabetical order according to their surnames, and each participant will be assigned a unique study number. After baseline measurement, randomisation will be conducted by an independent statistician off-site using a stochastic minimisation programme to balance the gender, age, and depression scores of the participants. Eligible participants will be randomised into two groups using a pre-/post-test waitlist control group design. The allocation to the two groups will be 1:1.

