### Statistical Methods

#### Statistical Methods for Primary and Secondary Outcomes

##### Data Analysis Plan

Data will be analysed by the SPSS for Windows, version 27. The normality of the primary outcome (depression) scores will be tested by the Kolmogorov-Smirnov test. If significant differences between sociodemographic variables are found, covariates will be used as a control or confounding variables in the main analysis. For Objective 1, multilevel modelling analysis will be used to investigate changes in the outcome measures (depression) at each time interval (2 weeks and 3 months) with respect to their baseline measurements to examine the effects of TPS. A two-level model will be built, with repeated time points at level 1 and respondents at level 2. The baseline difference between groups will be tested using the Wald test based on the regression coefficient estimates of the indicator. The changes in the outcome measures over time will be included in the fixed part of the model to estimate change from baseline to 2 weeks and from baseline to 3 months. To assess the effects of TPS over time, interaction terms will be included in the fixed part of the model. The significantly different demographics between groups identified in step one of the analysis and other possible confounders will be adjusted by including them in the main-effect model. The within-respondent random effects of the outcome measurements will be taken into account by the level-2 variance in the model. For Objectives 2, 3, and 4, pairwise comparison and other hypotheses on the intervention effects will be tested using a generalised Wald test with an adequate degree of freedom from the modelling analysis (70). The same model, which will be conducted separately for each outcome, will be used to investigate the effect of interventions on secondary outcome measures. To assess the effects of TPS, an intention-to-treat (ITT) analysis will be performed on all participants who undergo random allocation. A multiple imputation method will be used to handle missing data. The pooled results of the multilevel analyses with five multiple imputations will be presented. A sensitivity analysis will be performed by comparing results from analysis datasets with and without missing data imputation. In all tests, significant differences between groups will be detected with a 95% CI, and *p*-values of < 0.05 (two-tailed) will be considered significant. For Objective 5, the neurological rs-fMRI data, longitudinal VBM will be used to examine whether TPS produces local changes in grey matter. Specifically, relative local increases and decreases between pre- and post-intervention scans will be compared within and between study groups. The diffusion MR data will be analysed using the diffusion tensor model. After a mathematical diagonalization process, the eigenvectors and eigenvalues describing the tensor ellipsoid will be determined. Then, two standard diffusion indices will be obtained which are the following: (1) the apparent diffusion coefficient and (2) the fractional anisotropy. DTI scans pre- and post-treatment will permit the assessment of changes in axial diffusivity, with lower values being interpreted as the structural enhancement of white matter. For the cognitive data analysis, general linear modelling (GLM) will be used to compare the difference in performance in the forward and backward digit span, the Stroop test, the category verbal fluency test, and the TMT Parts A and B between the TPS group and the waitlist control group. Performance on the TMT between the TPS group and the waitlist control group will be analysed by one-way repeated-measures ANOVA. Participants' narrative feedback on TPS will be analysed with descriptive content analysis.

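### The only missing-data sensitivity analysis does not probe dropout that depends on unobserved depression scores, and five imputations leave avoidable simulation error in p-values near 0.05

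*Protocol article*

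**What the plan says.** The Data Analysis Plan in the protocol article sets the primary analysis of HAM-D-17 as a multilevel model: "A two-level model will be built, with repeated time points at level 1 and respondents at level 2". On missing data it says "A multiple imputation method will be used to handle missing data", then "The pooled results of the multilevel analyses with five multiple imputations will be presented", and it names one check: "A sensitivity analysis will be performed by comparing results from analysis datasets with and without missing data imputation". Significance is judged throughout at the usual level: "values of < 0.05 (two-tailed) will be considered significant".

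The separate section on non-adherence and missing data only repeats that multiple imputation will be used. The article does not name the assumed missingness mechanism, the variables in the imputation model, an expected dropout rate, a reason for choosing five, or what the with/without comparison is for. It does fix the number of imputations and the form of the sensitivity analysis. The point below concerns those two stated choices, not detail left for a later analysis plan.

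**The concern.** A missing-data sensitivity analysis is most useful when it varies the assumption most in doubt. Here that is whether, given the recorded data, the chance of a missing score is unrelated to the score itself. If both analyses in the comparison rely on that assumption, they can agree closely and both be wrong.

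Dropout related to unrecorded mood is plausible in this trial. Withdrawal of consent and deteriorating health are listed among the reasons for discontinuing the intervention. The limitations section warns that waitlist participants may treat themselves while waiting. The article describes participants as blinded, but the waitlist arm receives TPS only later, so those participants may well realise that they are waiting. Staying in follow-up could then depend on how a participant feels.

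The second issue is simulation error. With 30 participants and a 0.05 threshold, a result near the line could fall on either side depending on the random seed if only five imputed datasets are pooled.

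**Working it through.** **Inputs from the protocol article.** Total sample: "A total of 30 community-dwelling subjects, aged 18 and above, will be recruited" (Trial Design). Allocation: "The allocation to the two groups will be 1:1" (Randomisation, Allocation, and Masking), so 15 per arm. Alpha 0.05 two-sided, and five imputations (Data Analysis Plan). The sample size has no derivation to reproduce: "Therefore, we cannot base on their effect size to estimate our sample size in this study" (Sample Size Estimation). The five imputations have none either.

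**Assumed inputs.** The fraction of missing information (FMI) and the number missing are not in the article, so ranges are shown: FMI 0.05 to 0.3, and 1 to 5 of 15 per arm missing at the 3-month visit (7% to 33%).

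**Step 1: what each side of the comparison assumes.**
- Standard multiple imputation assumes missing at random, given the variables in the imputation model.
- A two-level model fitted by likelihood to all available visits assumes missing at random, given the variables in the analysis model.
- A completers-only analysis generally needs a stronger assumption.

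None of these lets missingness depend on the unobserved score.

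**Step 2: does agreement mislead?** This was simulated with 8,000 participants, three visits, SD 1, correlation 0.5 and a true 3-month effect of -0.75 SD. In the not-at-random case, worse 3-month scores were more often missing under TPS and better ones more often missing on the waitlist (16% and 22% missing). This is a deliberately adverse mechanism, chosen to test the comparison.

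| Mechanism | Imputation (large-sample equivalent) | Mixed model, available visits | Completers |
|---|---|---|---|
| Completely at random | -0.747 | -0.747 | -0.757 |
| At random | -0.748 | -0.755 | -0.752 |
| Not at random | -1.027 | -1.008 | -0.933 |

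In the last row the two likely planned analyses differ by 1.027 - 1.008 = 0.019 SD. They overstate the benefit by 1.027 - 0.75 = 0.277 and 1.008 - 0.75 = 0.258 SD. Completers are also off, by 0.933 - 0.75 = 0.183 SD.

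**Step 3: Monte Carlo error, approximate formula.** With m imputations, the SD of the pooled t statistic across seeds is about sqrt(FMI/m). Take t = 2.05 on 30 - 2 = 28 df, which gives p = 0.050, and move it by one SD each way.

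| FMI | m | SD of t | t range | p range |
|---|---|---|---|---|
| 0.05 | 5 | sqrt(0.05/5) = 0.100 | 1.95 to 2.15 | 0.040-0.061 |
| 0.1 | 5 | sqrt(0.1/5) = 0.141 | 1.91 to 2.19 | 0.037-0.067 |
| 0.2 | 5 | sqrt(0.2/5) = 0.200 | 1.85 to 2.25 | 0.032-0.075 |
| 0.3 | 5 | sqrt(0.3/5) = 0.245 | 1.81 to 2.29 | 0.029-0.082 |
| 0.2 | 50 | sqrt(0.2/50) = 0.063 | 1.99 to 2.11 | 0.044-0.057 |

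**Step 4: check by simulation.** The formula ignores noise in the estimated variance and degrees of freedom. Trials of 30 were therefore simulated with proper normal-model imputation, Rubin pooling and small-sample degrees of freedom. Datasets whose p-value with 2,000 imputations lay between 0.04 and 0.06 were re-imputed 400 times. The table gives 95% ranges of p across seeds, which are wider than one-SD ranges by construction.

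| Missing per arm | m = 5 | m = 50 | Seeds on minority side of 0.05, m = 5 / m = 50 |
|---|---|---|---|
| 1 of 15 | 0.029-0.094 | 0.042-0.059 | 37% / 17% |
| 2 of 15 | 0.021-0.126 | 0.037-0.064 | 41% / 24% |
| 3 of 15 | 0.017-0.161 | 0.033-0.067 | 42% / 26% |
| 5 of 15 | 0.009-0.218 | 0.028-0.078 | 44% / 32% |

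The minority-side shares apply only to datasets already selected to lie close to 0.05.

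**The case against.** The strongest reply is that the plan claims little. It says results will be compared. It does not call the comparison a test of missing at random and does not promise to declare robustness. Showing whether imputation changes the answer is a legitimate, limited check. This is correct, and it is why the comparison should stay.

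A reader might go further and infer that the comparison would look reassuring whatever the dropout mechanism, differing only by simulation noise. The documents do not support that. They do not say that the unimputed analysis uses all available visits. The abstract mentions repeated-measures ANOVA, and the cognitive outcomes use general linear modelling and repeated-measures ANOVA, which commonly drop incomplete cases. Nor do they say that the imputation model uses only the analysis variables; auxiliary baseline measures could separate the two results. In the simulation, completers differed from imputation by 1.027 - 0.933 = 0.094 SD, so the comparison is not empty. With five imputations, noise alone could also make the two p-values disagree. What stands is narrower: under no reading does the comparison probe not-at-random dropout.

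On size, the missing fraction is assumed. The article intends to keep participants who stop treatment in follow-up and plans message reminders, so little may be missing. At FMI 0.2, five imputations have relative efficiency of about 1/(1 + 0.2/5) = 96%, and sampling error dominates in a 30-person pilot. All of this is fair, and it confines the second half of the point to results near 0.05.

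**Conclusion.** The point holds in a limited form and deserves moderate weight. The one stated missing-data sensitivity analysis does not depart from missing at random in the direction that matters, so agreement between its two sides is not evidence against dropout driven by unobserved depression scores. In one adverse scenario the imputed and unimputed analyses agreed within 0.02 SD while both overstated the benefit by 0.26 to 0.28 SD. That shows what can happen; it is not a forecast for this trial.

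Five imputations leave seed dependence that is easy to remove, but it affects the conclusion only when the p-value lies near 0.05.

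The conclusion rests on three assumptions: that the methods named carry their standard missing-at-random interpretation, since the article states no mechanism; that some outcome data will be missing; and that the missing fraction lies in the range shown. With complete data neither half matters.

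**What to change.** In the Data Analysis Plan:

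1. Replace five imputations with at least 50, and record the seed. The larger number reduces the Monte Carlo error; the seed only makes the result reproducible.
2. Keep the with/without-imputation comparison, labelled as descriptive, and say whether the unimputed analysis uses all available visits or completers only.
3. Add a delta-adjusted multiple imputation analysis of HAM-D-17. Shift the imputed scores of TPS-arm dropouts towards worse outcomes over a range set in advance, and report the shift at which the conclusion changes. The article gives no basis for the range, so the investigators should justify it. Imputing separately within arms of about 15 is debatable and need not be part of the change.

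The cost is a little more programming and negligible computing time, with no new data and no change to trial conduct. The downside is that the result may look less robust.

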Dopamine (DA) is a neurotransmitter that plays an important role in learning, reward, motor control, emotion, and executive functions. Dysfunction of the frontal-striatal dopamine circuit is thought to be involved in depression (46). Thus, frontal-striatal connectivity is a target to manipulate DA activity in deeper brain regions and improve functions that rely on this circuit (47). Past studies used high-frequency repetitive TMS (rTMS) to stimulate the dorsolateral prefrontal cortex (DLPFC), which induced DA release in the ipsilateral caudate nucleus (48) or putamen (49). The DLPFC has dense connectivity with the anterior cingulate cortex (ACC) and the orbitofrontal cortex (OFC). Following high-frequency rTMS of the left DLPFC, there was an increase in DA levels in the ipsilateral ACC and OFC, but no changes occurred in the right DLPFC (50). These findings suggest that DA activity in the human frontal cortex can be manipulated by NIBS. Thus, in this study, we used TPS to probe the frontal-striatal network by targeting the left DLPFC. Apart from DA, it is evident that other neurotransmitters, such as excitatory and inhibitory neurotransmitters glutamate (Glu) and gamma-aminobutyric acid (GABA), are involved in the pathophysiology of MDD (51). Reduction in cortical Glu or GABA levels is associated with MDD. Studies have shown that reduced cortical GABA level is associated with dysfunctional GABAergic interneurons and GABA_A_ receptors, wherein affected GABAergic transmission is believed as a mechanism of MDD (52).

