**Secondary objectives**:

To improve young adults' anhedonia symptoms after the 2-week TPS intervention and will be maintained at 3-month post-intervention follow-upTo improve young adults' instrumental activities of daily living (IADL) after the 2-week TPS intervention and will be maintained at 3-month post-intervention follow-up.To improve young adults' cognition after the 2-week TPS intervention and will be maintained at 3-month post-intervention follow-up.Post-MRI scan will show a remarkable structural and functional connectivity in participants' brains after the 2-week TPS intervention compared to pre-MRI scan.

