#### Neuroimaging

Participants will receive pre- and post-treatment MRI scans to measure any changes in structural and functional connectivity changes in the brain. Structural MRI, diffusion tensor imaging (DTI), and resting state-fMRI (rs-fMRI) will be performed using a 3T scanner at the University Research Facility in Behavioural and Systems Neuroscience, The Hong Kong Polytechnic University. The subjects will be closely monitored by the research assistant and the radiographer during scanning. The whole scan will last around 45 min including preparation. Structural MRI scans, including T1- and T2-weighted fluid attenuation inversion recovery (T2-FLAIR) sequences, will be used for assessing regional volume differences across the whole brain. High resolution sagittal 3D T1-weighted [spoiled gradient recalled echo (SPGR)/magnetisation-prepared rapid gradient echo (MPRAGE)] images of 1 mm x 1 mm x 1 mm were acquired with repetition time (TR) = 1,820 ms, echo time (TE) = 3.75 ms, inversion time (TI) = 1,100 ms, and flip angle = 70°. This will be followed with axial 2D-T2-weighted FLAIR images of 0.9 × 0.9 × 3 mm, which will be acquired with TR = 9,160 ms, TE = 90 ms, TI = 2,500 ms, and flip angle = 150°, for the quantification of white matter hyperintensities (WMH). DTI sequence will be conducted using a single-shot spin-echo echo-planar imaging, with diffusion-sensitising gradients applied along 16 non-collinear directions with diffusion weighting factor b = 1,000 s/mm^2^ and two b = 0 images. The imaging parameters were the following: TR/TE = 1,200/82 ms, matrix size = 128 × 128, field of view (FOV) = 240 mm, slice thickness = 3 mm with no intersection gap, number of excitations = 2, and number of slices = 67. Finally, resting-state fMRI of 150 T2-weighted gradient echo-planar imaging (EPI) will be acquired with TR = 2 s and TE = 32 ms, with 32 slices, and a resolution of 3 × 3 × 4 mm, during which subjects will view a fixation cross (“+”) passively at the centre of the screen. Images processing and analysis will be performed using software packages including FSL (http://fsl.fmrib.ox.ac.uk/fsl/fslwiki/), Freesurfer, and SPM8 (Oxford, UK). Total brain and its total grey and white matter volumes will be extracted from the T1 structural scan. Grey matter and white matter tissue maps will be segmented and compared for regional tissue density differences using voxel-based morphometry (VBM) (69). Structural connectivity will be assessed by fractional anisotropy (FA) maps extracted from DTI imaging.

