
For functional connectivity, all resting state-fMRI (rs-fMRI) volumes will be pre-processed, with motion correction and slice timing correction, and then linearly registered to the Montreal Neurological Institute (MNI) standard space. A data-driven approach will be used for the analysis of rs-fMRI data. Independent component analysis will be done with Multivariate Exploratory Linear Decomposition in FSL. A set of independent components will be identified as the common resting-state functional networks. The global and local efficiency, modularity, and hubs will be computed using the Brain Connectivity Toolbox (https://sites.google.com/site/bctnet/). A dual regression approach will be used to investigate between-group differences in the individual functional networks. The significance threshold of the voxel-wise differences will be set at *p* < 0.05 (family-wise error corrected).

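### The Data Analysis Plan assigns the resting-state fMRI data to a grey-matter method, and the only functional-connectivity test stated has no pre-to-post term

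*Protocol article*

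**What the plan says.** The last of the Secondary objectives is a before-and-after statement: "Post-MRI scan will show a remarkable structural and functional connectivity in participants' brains after the 2-week TPS intervention compared to pre-MRI scan". The Neuroimaging section repeats that intent: "Participants will receive pre- and post-treatment MRI scans to measure any changes in structural and functional connectivity changes in the brain".

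That section then gives one method per type of data. After describing volumes taken from the T1 structural scan, it says: "Grey matter and white matter tissue maps will be segmented and compared for regional tissue density differences using voxel-based morphometry (VBM". Structural connectivity comes from fractional anisotropy maps. The resting-state fMRI data go to independent component analysis (ICA) and graph measures, and then: "A dual regression approach will be used to investigate between-group differences in the individual functional networks".

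The Data Analysis Plan, the only section that assigns analyses to numbered objectives, says something else: "For Objective 5, the neurological rs-fMRI data, longitudinal VBM will be used to examine whether TPS produces local changes in grey matter". It continues, for VBM, that "relative local increases and decreases between pre- and post-intervention scans will be compared within and between study groups", and then describes diffusion indices before and after treatment. It contains no functional-connectivity analysis.

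On scan timing, the Abstract and Trial Design place the fMRI before and after the six TPS sessions for the subjects of each group. Intervention Description says that the waitlist group also receives those six sessions.

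**The concern.** Two things do not fit together. First, the section that a trial statistician would follow for Objective 5 names the functional data but attaches a structural method to them. VBM compares local tissue density or volume, so it cannot answer a question about functional connectivity.

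Second, the objective is change, whereas the stated functional test is a difference between groups. The text does not say whether that means post-treatment scans, both scans pooled, or change from the first scan to the second. These are different estimands with different precision.

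At stake is whether the functional half of Objective 5 gets a fixed, interpretable estimate. The choice of contrast could otherwise be made after the scans have been examined.

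**Working it through.** The documents state no effect size, standard deviation or power for the imaging outcome, so there is no planned figure to reproduce. The main check compares the sections.

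**1. Which data feed VBM?**
- Neuroimaging: segmented grey and white matter tissue maps, described with the T1 structural scan.
- Data Analysis Plan: the resting-state fMRI data.
- These conflict. Only the Neuroimaging description fits what VBM measures.

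**2. Which method analyses the resting-state data?**
- Neuroimaging: ICA, graph measures and dual regression.
- Data Analysis Plan: longitudinal VBM and nothing else.
- These conflict. The structural half of Objective 5 is covered by VBM and the diffusion indices. The functional half has no valid analysis in this section.

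**3. Is the functional test a test of change?**
- Secondary objectives and the opening of Neuroimaging: before against after.
- Dual-regression sentence: between groups, with no time point, change score or group-by-time term.
- Data Analysis Plan: interaction terms for depression and a before/after contrast for VBM. The article does state such terms elsewhere.

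**4. Does the choice of contrast matter?** This is an illustration for one pre-chosen measure. The inputs are 30 subjects at 1:1, so n = 15 per arm, and two-sided alpha of 0.05. The correlation r between a subject's two scans is my assumption.
- Post-treatment scans only, 80% power, normal approximation: detectable difference = (1.96 + 0.84) × √(2/15) = 1.02 SD (1.06 by the exact t distribution).
- Change score: multiply by √(2(1 − r)).
- Baseline-adjusted: multiply by √(1 − r²).

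| r | Change score | Baseline-adjusted |
|---|---|---|
| 0.3 | 1.21 | 0.98 |
| 0.5 | 1.02 | 0.89 |
| 0.7 | 0.79 | 0.73 |
| 0.8 | 0.65 | 0.61 |

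- Both scans pooled, r = 0.5: a true post-treatment difference of 0.8 SD becomes 0.8/2 = 0.4, with SD √((1 + 0.5)/2) = 0.87. Power is about 24%, against 59% for post-treatment scans only.

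The reading of the sentence therefore changes what can be detected. Voxel-wise correction would lower all these powers.

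**5. Which waitlist scans enter the contrast?** Let TPS change a measure by δ in either arm, and ignore drift over time.
- Waitlist pair spans the untreated wait: expected contrast = δ − 0 = δ.
- Waitlist pair brackets the group's own TPS: expected contrast = δ − δ = 0, whatever δ is.

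Read literally, the Abstract and Trial Design allow the second case. Explanation for the Choice of Comparators, which compares treated with untreated subjects at the same time points, implies the first. A change term alone does not settle this.

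**The case against.** The best defence is that the Neuroimaging section already gives a workable functional method and makes clear that VBM belongs to structural data. On that view the Data Analysis Plan contains a one-sentence slip in a secondary outcome of a small pilot. Intent to analyse change is stated at the start of Neuroimaging, and the increases-and-decreases sentence might be meant to cover all of Objective 5. Much of this stands: a reader can work out what was probably meant. It does not remove the contradiction, because the section that assigns methods to objectives names the wrong one. That the sentence covers more than VBM is a guess.

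Three stronger inferences are tempting, and the documents do not support them.
- *The imaging does not measure what the trial targets.* Biological Mechanism of TPS does say that "in this study, we used TPS to probe the frontal-striatal network by targeting the left DLPFC", and no outcome or analysis names that circuit. But Objective 5 promises connectivity in general. Whole-brain ICA with dual regression measures functional connectivity and does not exclude frontal or striatal components. A list of seeds or networks may also stand in a fuller document that is not shown.
- *The test excludes change.* The dual-regression sentence is silent on time. It specifies neither a post-only nor a pooled comparison.
- *The false-positive risk is 34% to 46%.* That range is 1 − 0.95^k for k = 8 to 12 independent tests, made up of four graph measures plus an assumed 4 to 8 networks. The article gives no number of networks, says only that the graph measures are computed, and offers no basis for independence. The range is an illustration, not a property of this plan.

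**Conclusion.** The point holds in a limited form. The Data Analysis Plan assigns the resting-state data of Objective 5 to a method that yields no functional-connectivity value, and this contradicts Neuroimaging. The one functional test stated does not carry the before/after contrast that the objective requires. Both follow from the text without any assumption.

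The size is modest: one half of one secondary objective is affected, and the primary depression outcome is not. The power figures above depend on an assumed correlation and show only that the choice of contrast is not neutral. The waitlist timing problem is conditional. If the waitlist pair brackets that group's own TPS, the between-arm change contrast cannot estimate a treatment effect; if it spans the wait, it can.

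That no frontal-striatal endpoint is named is a matter of pre-specification, on which a suggestion is reasonable but a requirement is not.

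**What to change.** 1. In the Data Analysis Plan, tie longitudinal VBM to the T1 structural scans and assign the resting-state fMRI data to the ICA, graph and dual-regression analysis described under Neuroimaging.
2. State that functional analysis as a between-arm comparison of within-subject change from the first scan to the second, using difference maps or a group-by-time term.
3. Reconcile the Abstract and Trial Design with the comparator section, and say that the waitlist scan pair used in this contrast is the one that spans the untreated waiting period.
4. Optionally, since the rationale points to the frontal-striatal network through the left DLPFC, name that connectivity as the leading imaging contrast and label the other ICA and graph results exploratory. The price is that findings outside the named circuit carry less weight.

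Items 1 and 2 cost only wording. Item 3 also costs only wording if the untreated waitlist pair is part of the scan schedule. If it is not, each waitlist participant (15 under 1:1 allocation) would need a further scan before starting TPS, or the between-arm claim must be given up. Trial Status reports that recruitment is complete but not whether scans have been taken. The amendment should therefore be dated and should state whether imaging data had been examined.
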